##### Risk model construction

Using deep-learning-based artificial intelligence technology, we will develop an early risk assessment model for the impact of maternal inflammation on infant brain development. This model will be able to integrate data on maternal inflammation during pregnancy to predict the brain development of children with high precision and further identify potential risks in infant intelligence, motor skills, emotions, and cognition. Through rigorous training and validation, our goal is to ensure that the area under the curve (AUC) of the model's recognition ability for relevant developmental disorders reaches 0.8 or above.

##### Gene-environment interaction

Integrate the results of whole-exome sequencing to identify genes crucial for early-life brain development. Through in-depth genetic and statistical analyses, this study will explore how these genes interact with maternal inflammation and environmental exposure during early life. This study anticipates uncovering at least 10 genes that show significant interaction effects and elucidating the underlying molecular mechanisms.

#### Secondary outcome

In the secondary results of this study, we will mainly conduct an in-depth exploration of the impact of environmental factors on children's brain development from two aspects, namely the maternal environmental exposure during pregnancy and the family environment and parenting patterns after birth.

##### Research plan on the impact of maternal adverse factor exposure during pregnancy on infant early brain development

Focusing on maternal exposure to inflammation during pregnancy, this plan aims to analyze its mechanism of action on infant early brain development. On the one hand, we will study the correlation between the changes in inflammatory indicators during pregnancy and infant brain development. By comparing the brain imaging and electrophysiological data of children under different inflammatory levels, as well as the development of children's intelligence, cognitive ability, motor ability and other abilities, we will explore the potential impact of maternal inflammation during pregnancy on the development of brain structure and function. On the other hand, regarding other adverse conditions during pregnancy, such as chorioamnionitis, placental pathological abnormalities, gestational diabetes mellitus, gestational hypertension and other pregnancy-related diseases, as well as adverse environmental exposure during pregnancy, we will analyze their impacts on the structure and function of infant brains, and the potential links between such impacts and the future development of infants in terms of intelligence, cognition, emotion, and motor skills.

##### Research plan on the impact of family environment and parenting patterns after birth on infant brain development

This study will conduct research on the family environment and parenting patterns after birth, and analyze their impacts on the structure and function of infant brains. With the help of professional assessment scales, this study will explore the relationship between family parenting patterns and infant brain development, paying particular attention to the promoting or inhibiting effects on intellectual development and the underlying pathways. At the same time, this study will examine the impact of the family environment on infant emotional regulation ability, as well as the differences in infant cognitive development under different parenting styles, and further explore the potential neural mechanisms through which these factors affect infant brain functions.

#### Data analysis

##### Cohort and data objectives

Conduct an integrity assessment of the “gene-environment-electroencephalogram (EEG)—imaging-behavior” multimodal data for the included cohort of infants and toddlers aged 0–3 years. Calculate the integrity of core data such as questionnaire data, gene data, and children's behavior data, with an integrity rate of at least 90%. For data with high noise levels such as brain magnetic resonance imaging (MRI) and EEG, the integrity rate should be ≥85%, and the overall integrated integrity should be ≥80%. Examine the reasons for missing data. For completely random missing data of different types, use methods such as multiple imputation, k-nearest neighbors (KNN) imputation, the Generative Adversarial Imputation Network (GAIN) algorithm, and expert judgment filling to supplement the data. Filter gene data through the Genome Analysis Toolkit (GATK), annotate it with ANNOVAR, and screen high-quality loci through the Hardy-Weinberg Equilibrium (HWE) test. Remove outliers from environmental data regarding inflammatory indicators during pregnancy, pregnancy complications, and family parenting scales. Process MRI structural images using Free Surfer/FSL and functional magnetic resonance imaging (fMRI) using Statistical Parametric Mapping (SPM) for imaging data. Preprocess EEG data using EEGLAB. Transform behavior data into Z-scores. Present demographic characteristics through descriptive statistics. Use the chi-square test/analysis of variance to compare baseline differences among subgroups such as gender and gestational age to ensure the balance of the cohort and lay the foundation for subsequent analyses.

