#### Follow-up plan

Utilizing an aggregation cross design, referencing the grouping methodology of the Baby Connectome Project (BCP) by UNC/UMN in the USA (12), participants were categorized into 9 sub-cohorts based on the age at initial enrollment, each having varying sampling density and age spans (Table 1). Each of the first three sub-cohorts enrolled 536 participants, while sub-cohorts 4–9 each enrolled 268 participants, totaling 3,216 participants. Each participant was followed up 3–4 times, yielding data from 11,256 participant—visits. Moreover, the follow-up intervals for sub-cohorts 1–3 and 4–9 were 3 and 6 months, respectively, ensuring sufficient sampling density during the first year, which is critical for rapid development in language and socio-emotional skills. Oversampling was strategically implemented during milestones of language and socio-emotional development and periods prone to scan failures (before the age of 3). Considering the low cooperation levels of infants and potential dropouts, 3,847 participants were recruited to ensure the acquisition of high-quality data from 3,216 subjects (Figure 1).

**Table 1 T1:** Cohort design and follow-up time planning schedule.

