**Aggregated cross design**						
**Cohort number**	**Number**	**Follow-up**				**Note**
		**First**	**Second**	**Third**	**Fourth**	
1	536	0	3	6	9	High-density sampling: once every 3 months
2	536	1	4	7	10	
3	536	2	5	8	11	
4	268	10	16	22		Medium-density sampling: every 6 months
5	268	6	12	18		
6	268	9	15	21		
7	268	12	18	24		
8	268	15	21	27		
9	268	24	30	36		
Total	3,216	Number of Participant—visits: 11,256			
Target number	3,847	Considering the failure rate of magnetic resonance imaging and the dropout rate of the cohort, the effective enrollment was guaranteed to be >11,256 cases				

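### The only stated imputation rule is tied to completely random missingness and lets single or expert-judged fills stand in for multiple imputation, which can make standard errors too small

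*Protocol article*

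**What the plan says.** The rule stands in the protocol article under Data analysis, Cohort and data objectives. It opens with an instruction to "Examine the reasons for missing data", but nothing is made to depend on the answer. It continues "For completely random missing data of different types, use methods such as multiple imputation, k-nearest neighbors (KNN) imputation", and the list ends with "the Generative Adversarial Imputation Network (GAIN) algorithm, and expert judgment filling to supplement the data". The four methods are unranked, and the text does not say which serves inference and which serves preparation of model inputs.

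The same paragraph sets completeness targets of at least 90% for questionnaire, genetic and behavioural data, at least 85% for MRI and EEG, and at least 80% overall.

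Other sections describe how data are expected to be lost:

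- Follow-up plan: oversampling covers "periods prone to scan failures (before the age of 3" (years), and "Considering the low cooperation levels of infants and potential dropouts, 3,847 participants were recruited to ensure the acquisition of high-quality data from 3,216 subjects".
- Table 1, target row: "Considering the failure rate of magnetic resonance imaging and the dropout rate of the cohort".
- Brain imaging data and Table 3: scans are done without sedation and total 40 minutes, and a supplementary block is run only if the infant stays asleep.

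**The concern.** The condition attached to the rule is the one least suited to this design. If values really are missing completely at random, an analysis of the observed outcomes is already unbiased, and filling them in adds little. The losses that the article expects come from how an infant behaves in the scanner, and that need not be unrelated to age, sleep, regulation or development.

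The list also treats unlike things as alike. Multiple imputation carries the uncertainty of the missing values into the standard error. A nearest-neighbour or adversarial-network fill completed once does not, and neither does a value entered by an expert. The text gives the expert no model, no measure of uncertainty and no blinding rule, in a study that compares children by maternal inflammation. At stake are the group comparisons, the correlations of brain measures with inflammatory markers, and the interaction tests.

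**Working it through.** The article gives no figure for this point, so none has to be reproduced. The check asks how much is missing and what each listed option does to a test at a nominal two-sided 5% (two-sided is an assumption).

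**1. Amount missing.** Table 1 is consistent: 3×536 + 6×268 = 3,216 children and 3×536×4 + 6×268×3 = 6,432 + 4,824 = 11,256 visits. The recruitment margin implies a loss of 1 − 3,216/3,847 = 16.4%; no rate is stated. The completeness targets allow 15% for MRI and EEG and 20% overall. So 15-20% is the relevant range.

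**2. Formula for a single fill.** Let a fraction f of outcomes be replaced by the predicted mean within group. The true standard error stays that of the observed cases, proportional to σ/√(n(1−f)). The reported one is about σ√(1−f)/√n, because filled values add no residual scatter but are counted in n. The ratio of reported to true is √(1−f)×√(1−f) = 1−f. Hence type I error = 2×[1−Φ(1.96×(1−f))]:

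- f = 0.15: 2×[1−Φ(1.666)] = 9.6%
- f = 0.164: 2×[1−Φ(1.639)] = 10.1%
- f = 0.20: 2×[1−Φ(1.568)] = 11.7%

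The sample size does not enter.

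**3. Simulation.** Assumptions: no true group effect, 200 children per group, age uniform over 0-3 years and included in the analysis model, 1,500 replicates, 5 nearest neighbours matched on group and age, and 20 imputations combined by Rubin's rules.

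| Missing | Mechanism | Single nearest-neighbour fill | Multiple imputation | Complete cases |
|---|---|---|---|---|
| 15% | completely random | 8.6% | 4.3% | 4.3% |
| 15% | depends on age | 9.3% | 5.1% | 5.2% |
| 20% | completely random | 11.8% | 4.8% | 4.7% |
| 20% | depends on age | 11.9% | 4.4% | 4.7% |

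The single fill reports standard errors about 13-19% too small. Bias is about zero for every method in these four rows. A second set-up (180 per group, an auxiliary variable with R² 0.3, neighbours within group, 4,000 replicates) gives 8.2% and 9.5% at 15% and 20% missing. Together these give the range of about 8-12%.

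**4. If neighbours ignore group.** The filled values then carry no group difference. Estimate and reported standard error both shrink by about 1−f, so type I error stays near 5%, but a true effect is diluted by roughly the missing fraction, here 15-20%. The article does not say how neighbours are chosen.

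**5. If failure depends on the outcome.** Suppose that in exposed children only, the log-odds of failure rise by 0.8 for each SD of lower age-adjusted outcome. This is an assumption. Every method is then biased by 0.12 SD (15% missing) to 0.15 SD (20%). Type I error is 28% and 41% with the nearest-neighbour fill, and still 19% and 27% with multiple imputation. Here a better imputation method does not remove the bias, and only a sensitivity analysis can show how far the conclusion depends on the mechanism.

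**The case against.** The strongest reply is that the sentence states a condition, not an assumption: the reasons for missingness are examined first, and the listed methods then apply only to values found to be completely random. On that reading nothing is prescribed for non-random scan failures, and their handling may stand in the full protocol or analysis plan, which is not shown. This is fair, and silence on other mechanisms is not held against the article. But the harm in steps 2 and 3 arises when the condition is met, so the reply does not reach it.

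Second, multiple imputation is listed first, and the reference to different types of data may mean that each type gets a suitable method. Nothing says that nearest-neighbour or adversarial fills complete outcomes that are then tested. This stands in part: the inflation depends on the option taken. The fault is that the text permits any of them without a rule.

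Third, a reader might infer that the article says scan failure depends on age, temperament, development or maternal inflammation, and that estimates will therefore be biased. The documents do not support that. The period named as prone to failure, before age 3, spans the whole cohort. Cooperation is mentioned only in general terms. The Weakness section names moving away as the cause of loss, which could be close to random. Failure that depends on age alone causes no bias once age is modelled.

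Fourth, a reader might infer that risk-model targets will be filled in and the AUC inflated. The article does not say that targets are imputed, so this remains a risk to rule out.

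**Conclusion.** The point holds as a defect in a stated method. The rule is conditioned on a mechanism that sits poorly with the losses the study expects, and it places expert judgement and single fills on a level with multiple imputation.

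The firm consequence is understated uncertainty: type I error of about 8-12% in place of 5% at the 15-20% missingness that the plan tolerates. This rests on three assumptions: outcomes are filled once, neighbours are matched on group, and the completed data are analysed as observed. It does not need the missingness to be non-random.

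Bias is possible, not established. It needs failure to be related to outcome or exposure beyond the modelled covariates. That is plausible for unsedated infant scanning, but it is an assumption that the article does not state, and the figures in step 5 only illustrate it. The rule should be changed before analysis.

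**What to change.** Replace the imputation sentence with text to this effect:

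- Missing values are assumed missing at random given age, sub-cohort, sex, gestational age, maternal inflammation, standardised developmental score, ASQ:SE-2, the infant sleep questionnaire, and earlier scans where they exist.
- Inference uses likelihood-based mixed models, or multiple imputation (at least 20 sets) with these variables and Rubin's rules.
- Nearest-neighbour and adversarial-network fills are confined to inputs of the risk model and are fitted inside training folds.
- Outcome labels for the risk model are not imputed.
- Expert judgement filling is removed.
- A delta-adjusted sensitivity analysis covers non-random scan failure.

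The covariates are chosen because they are available at all ages. In Table 2 the developmental score comes from the Griffiths scales up to 24 months and the Wechsler scale from 25 months, and the article already plans Z-scores. Temperament should not be required: its scale starts at 13 months, and sub-cohorts 1-3 (3×536 = 1,608 of 3,216 children, half the cohort) are seen only up to 11 months.

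The cost is analysis wording, some extra computing and slightly wider confidence intervals. No new data collection is needed.

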## Methods and analysis

### Research subject

The study subjects were infants and children aged 0–3 years and their mothers, and the Xiamen Children's Brain Development Cohort recruited the study subjects from the society (kindergartens, elementary schools, and other institutions) and the neonatal department of Xiamen Children's Hospital. Based on the information of the mothers' pregnancy—related medical history, infants whose mothers had high inflammatory indices during pregnancy (e.g., CRP, interleukin−1β, interleukin−6, interleukin−10, and macrophage inflammatory factor−1β), or had chorioamnionitis, pathologic abnormalities of the placenta, preterm premature rupture of the membranes, or had combined gestational hypertension and diabetes mellitus with maternal inflammatory diseases were included in the observation group. Infants without maternal inflammation were the control group.

Characteristics of our included subjects included:(1) age 0–3 years;(2) gestational age 37–42 weeks;(3) birth weight >2.5 kg; and(4) no significant birth complications. Characteristics of excluded subjects included:(1) history of resuscitation from asphyxia at birth;(2) congenital structural anomalies;(3) presence of inborn inherited metabolic disorders such as phenylketonuria, galactosemia, and congenital hypothyroidism;(4) presence of a major medical condition affecting growth, or development; and(5) contraindications to magnetic resonance imaging (MRI).

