##### Gene-environment interaction

In the data analysis of gene–environment interactions, this study will be base on whole exome sequencing data. First, variant detection and quality control will be performed using the Genome Analysis Toolkit (GATK). ANNOVAR will be utilized for functional annotation of the variants, and high-quality loci will be screened through the Hardy-Weinberg Equilibrium (HWE) test. We will focus on the variants of candidate genes related to brain development and loss-of-function mutations. Subsequently, the Sequence Kernel Association Test with Optimal weighting (SKAT-O) will be employed to analyze the association between gene sets and brain development phenotypes. Meanwhile, a generalized linear model will be constructed, incorporating pregnancy inflammation indicators (such as CRP and IL-6 levels), environmental exposure variables, and their interaction terms with gene variants to test the gene–environment interaction effects. By referring to the literature in fields such as neural synapse development and inflammatory signaling pathways, genes with significant effects in the interaction will be screened out. For the screened genes, methods such as metabolomics and proteomics will be further used to verify their regulatory mechanisms in brain development, analyze the impact of genes on the early-life brain structure and function of infants, and ultimately reveal the molecular pathways through which the interaction of genes, pregnancy inflammation, and environmental exposure affects early brain development. It is expected to identify at least 10 key genes with significant effects and clarify their potential biological mechanisms.

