##### The impact of family environment and parenting patterns on brain development

Regarding the secondary research results, we will conduct a comprehensive analysis from two aspects: the exposure of adverse factors in mothers during pregnancy and the family environment and parenting patterns after birth. For maternal exposure to adverse factors during pregnancy, on the one hand, regarding the correlation between inflammatory indicators and brain development, we will conduct correlation analysis between brain indicators such as MRI-derived brain volume, cortical thickness, and EEG power spectral density, and the levels of inflammatory cytokines such as C-reactive protein (CRP) and Interleukin-6 (IL-6). Group children according to the inflammatory levels and compare their brain imaging, electrophysiological data, and scores of relevant abilities of children. On the other hand, for other adverse conditions during pregnancy, conduct regression analysis to explore the potential links with the future development of children. In the analysis of family factors after birth, first conduct correlation and regression analysis between the scores of the quantified family parenting scale and brain indicators such as MRI-derived brain volume, cortical thickness, and EEG power spectral density. At the same time, explore the pathways through which parenting patterns affect children's intellectual development through mediation analysis. In addition, associate family environment variables with children's emotional regulation indicators, and compare the differences in children's cognitive development under different parenting styles.

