## Preliminary results

Between December 2021 and May 2024, 360 pairs of pregnant women and their offspring were recruited into the Xiamen Childhood Brain Development Cohort, which investigated basic family information through a baseline questionnaire, children's births through medical information, and MRI scans of children's brains who entered the cohort. Of the 360 children enrolled in the study (Table 4) , 203 (56.39%) were males, the mean gestational week of the mother's pregnancy was 35.67 weeks, the mean age of the children at MRI was 3.28 weeks, and there were a total of 163 (45.3%) children born at term and 156 (43.3%) children born by normal delivery.

**Table 4 T4:** Baseline characteristics and risk factors of research subjects.

**Variable**	**Sum mean (sd)**	**Male mean (sd)**	**Female mean (sd)**	** *p* **
People (%)	360	203 (56.39)	157 (43.61)	
Gestational age (week)	35.67 (3.88)	35.85 (4.03)	35.45 (3.68)	0.332
Age at scanning (week)	3.28 (3.30)	3.25 (3.49)	3.31 (3.05)	0.849
Full-term infant (%)	163 (45.3)	102 (50.2)	61 (38.9)	0.041
Birth weight (g)	2.49 (0.87)	2.58 (0.87)	2.37 (0.85)	0.024
Vaginal delivery (%)	156 (43.3)	97 (47.8)	59 (37.6)	0.067
Parity (%)				0.141
0	55 (15.3)	30 (14.8)	25 (15.9)	
1	163 (45.3)	84 (41.4)	79 (50.3)	
≥2	142 (39.4)	89 (43.8)	53 (33.8)	
Chorioamnionitis (%)	7 (1.9)	4 (2.0)	3 (1.9)	1.000
Gestational hypertension (%)	40 (11.1)	18 (8.9)	22 (14.0)	0.170
Gestational diabetes (%)	76 (21.1)	38 (18.7)	38 (24.2)	0.257
Pathological placental abnormalities (%)	7 (1.9)	2 (1.0)	5 (3.2)	0.265
Premature rupture of membranes (%)	47 (13.1)	25 (12.3)	22 (14.0)	0.752
Eclampsia (%)	27 (7.5)	13 (6.4)	14 (8.9)	0.486
Sexually transmitted diseases (%)	28 (7.8)	15 (7.4)	13 (8.3)	0.909
Antibiotic treatment (%)	68 (18.9)	34 (16.7)	34 (21.7)	0.297
Maternal inflammatory (%)	187 (51.9)	94 (46.3)	93 (59.2)	0.020

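### Outlier removal with no stated rule is ordered on the exposure variables themselves, and usual raw-scale rules would discard the highest inflammation values and flag rare complications

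*Protocol article*

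**What the plan says.** The cleaning steps under Data analysis, Cohort and data objectives, include: "Remove outliers from environmental data regarding inflammatory indicators during pregnancy, pregnancy complications, and family parenting scales". The sentence gives no definition of an outlier, no scale, no check separating errors from genuine values, and no comparison with and without the removed data.

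The same variables carry the study question elsewhere in the article:

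- Research subject places in the observation group "infants whose mothers had high inflammatory indices during pregnancy" (CRP, IL-1β, IL-6, IL-10 and a macrophage inflammatory factor are the examples), along with infants of mothers with complications such as chorioamnionitis or placental pathology.
- The first secondary-outcome plan studies inflammation level and also "other adverse conditions during pregnancy, such as chorioamnionitis, placental pathological abnormalities, gestational diabetes mellitus, gestational hypertension".
- The section on family environment and parenting patterns says "we will conduct correlation analysis between brain indicators such as MRI-derived brain volume, cortical thickness, and EEG power spectral density" and cytokine levels, and then: "Group children according to the inflammatory levels and compare their brain imaging, electrophysiological data, and scores of relevant abilities of children".
- Gene-environment interaction says "a generalized linear model will be constructed, incorporating pregnancy inflammation indicators (such as CRP and IL-6 levels") with gene interaction terms.

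No section protects genuine high values or recorded diagnoses from the removal step.

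**The concern.** Outlier removal is harmless when it catches unit or entry errors. Here it is aimed at the exposure. Inflammatory markers are typically right-skewed, so a cut-off set on the raw scale falls only on the upper tail, where maternal inflammation is clearest. Losing that tail narrows the exposure range, which can pull group contrasts and correlations toward zero and costs information in any dose-response or interaction analysis.

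Complications are yes/no records. A distributional rule applied to them can do only one thing to a rare condition: flag every case.

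Because no rule is fixed, the choice could also be made after the data are seen, with materially different results.

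**Working it through.** **Plan's own figures.** The plan gives no cut-off and no marker distribution, so there is no stated removal figure to reproduce. The complication counts come from Table 4 ("Of the 360 children enrolled in the study"): chorioamnionitis 7, placental abnormality 7, eclampsia 27, gestational hypertension 40, premature rupture of membranes 47, gestational diabetes 76. The printed percentage for the first reproduces: 7/360 = 1.9%.

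**Markers: assumptions, not from the document.** Lognormal marker with log-SD s = 0.8, 1.0 or 1.2. One SD of the marker (log or raw scale) shifts the outcome by −0.15 SD, so r = −0.15. The contrast is top quartile versus rest, with the quartile cut held at its value before removal.

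*Share removed, raw-scale 1.5×IQR.* Q1 = exp(−0.6745s), Q3 = exp(0.6745s), upper fence = Q3 + 1.5(Q3 − Q1).
- s = 0.8: fence 1.715 + 1.5 × 1.132 = 3.414; ln(3.414)/0.8 = 1.535; upper-tail share 6.2%.
- s = 1.0: fence 1.963 + 1.5 × 1.454 = 4.143; ln = 1.422; share 7.8%.
- s = 1.2: fence 2.247 + 1.5 × 1.801 = 4.949; ln(4.949)/1.2 = 1.333; share 9.1%.

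The lower fence is negative in each case (for s = 1.0, 0.509 − 2.180 = −1.67), so no low value is removed.

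*Share removed, raw-scale 3 SD.* At s = 1.0 the mean is 1.649 and the SD 2.161, so the cut is 8.13; ln = 2.096; share 1.8%. Across s it is 1.6–1.9%.

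*Effect on the contrast and correlation* (simulation, 1,000,000 draws; ranges over s):

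| Rule | Values removed | Top quartile lost | Contrast shrinks, effect log-linear | Contrast shrinks, effect linear in raw marker |
|---|---|---|---|---|
| 1.5×IQR, raw scale | 6–9%, all high | 25–37% | 14–19% | 31–51% |
| 3 SD, raw scale | about 2%, all high | 6–8% | 5–6% | 16–23% |
| Either rule, log scale | 0.3–0.7%, about half high | 0.5–1.4% | 1–2% | 3–10% |

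Closed-form check at s = 1.0, 1.5×IQR, log-linear effect: before removal, 0.3178/0.25 + 0.3178/0.75 = 1.695; after, (0.3178 − 0.1452)/(0.25 − 0.0776) + 0.3178/0.75 = 1.425; shrinkage 1 − 1.425/1.695 = 16%. The simulated value was 0.253 to 0.211, or 17%.

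The correlation falls from −0.15 to between −0.127 and −0.132 (log-linear) or −0.045 and −0.086 (raw-linear) under raw-scale 1.5×IQR, and to about −0.14, or −0.08 to −0.11, under raw-scale 3 SD.

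*Regression slope.* It stayed between −0.147 and −0.152 under every rule: selecting on the exposure does not bias a correctly specified slope. Precision is lost. At s = 1.0, raw-scale 1.5×IQR, log-scale analysis, the retained variance of the log marker is 1 − 1.422 × 0.1574 − 0.1574² = 0.751 (with 0.1574 = 0.1452/0.9224). Information kept is 0.922 × 0.751 = 69%. Across s it is 66–73%.

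**Complications: no distribution needed.** With prevalence p, a case has z = √((1 − p)/p).
- 7/360: √(353/7) = 7.1
- 27/360: √(333/27) = 3.5
- 40/360: √(320/40) = 2.8
- 47/360: √(313/47) = 2.6
- 76/360: √(284/76) = 1.9

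A 3 SD rule flags every case of the first two prevalences and none of the last three. All of them lie below 25%, so both quartiles are 0, the IQR is 0, and an IQR rule flags every case of every one.

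**The case against.** The strongest reply is that the sentence sits in a list of routine cleaning steps and fixes no rule. A check limited to unit, entry or assay errors fits the words equally well, and a full protocol or analysis plan may define it. That stands to this extent: a reader might infer that the plan deletes the most exposed mothers, and the document does not say so. It is a likely result of common raw-scale rules, not a stated one. But the instruction to remove is itself in the text, and it names the complications explicitly.

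Other parts of the reply also stand:

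- A reader might infer that any distribution-based rule takes only high values. On the log scale it does not, and it removes very little.
- A reader might infer that every effect is diluted. The gene-environment model and the planned regressions, if correctly specified, are not biased. The attenuation concerns the correlations and group comparisons, which belong to the secondary outcomes.
- The text removes data values. Since several markers or diagnoses can place a child in the observation group, losing one value need not remove the pair or change its group.
- The top-quartile contrast is illustrative; the plan does not define its level groups. Taking the top 51.9% as exposed (the Table 4 share with maternal inflammation), under the same lognormal model, gives shrinkage of 10–14% (log-linear) or 26–45% (raw-linear) for raw-scale 1.5×IQR, and 3–4% or 13–19% for 3 SD.
- It is unlikely that anyone would knowingly apply a z-score rule to a diagnosis the study sets out to analyse, and Table 4 still shows all 7 cases of each of the rarest conditions. Nothing shows that cases will be deleted. The wording nevertheless calls for removal from that variable, where it has no sensible meaning.

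**Conclusion.** The concern holds in limited form. The plan orders outliers removed from variables that define the exposed group and are its exposures, without a rule and without protecting genuine values. Under ordinary raw-scale rules the marker values lost are the highest ones, about 2% (3 SD) to 6–9% (1.5×IQR). High-versus-rest contrasts are then attenuated by about 5–19% if the effect is log-linear and 16–51% if it is linear in the raw marker, depending on rule and log-SD. The upper end is a worst case, not an expected loss. Regression and interaction slopes lose precision only, provided the model is correctly specified. These sizes rest on assumed lognormal markers and an assumed correlation of −0.15; the document supplies neither. The finding for yes/no complications rests only on the Table 4 counts and on which rule is applied.

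**What to change.** Replace the sentence with:

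> Values are set to missing only for a documented recording, unit or assay error or an impossible value, judged without knowledge of outcome. Genuine extreme values and all recorded complications are retained. Skewed markers are analysed on a log scale or by robust methods. Results with and without any exclusion are reported.

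Apply the same rule to the parenting scales. The child-care environment index, for example, is bounded at 0 to 13 and the article treats scores of 10 or below as its worst group, so a low in-range score is information and not an error.

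Cost: one sentence in the analysis section and one sensitivity run. No change to data collection.
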